### Outcome measures

The primary outcome is the proportion of patients in both treatment groups with a postoperative refraction in the second eye that deviates ≤1.0 D from target refraction 4 weeks after cataract surgery of the second eye. This is an accepted norm to define success in terms of refractive outcomes after cataract surgery [7, 28].

Secondary outcomes will include:
**Refraction**: the proportion of patients in both treatment groups with a postoperative refraction in the second eye that deviates ≤0.5 D from target refraction 4 weeks after cataract surgery of the second eye.**Visual acuity**: ETDRS, uncorrected and corrected distance visual acuity in LogMAR (the Logarithm of the Minimum Angle of Resolution), 1 week after first-eye surgery and 4 weeks after second-eye surgery, corrected for baseline visual acuity. In addition, the proportion of patients with a final corrected distance visual acuity (CDVA) of ≤0.1 LogMAR (measured at 4 weeks after second-eye surgery) will be compared for ISBCS and DSBCS.**Complications**: the number of intraoperative and postoperative complications within 3 months after first-eye surgery.**Patient-reported outcome measures (PROMs)**, including patient satisfaction, vision-specific quality of life, and health-related quality of life:
Vision-specific quality of life and patient satisfaction will be measured using the National Eye Institute Visual Function Questionnaire-25 (NEI VFQ-25) [37] and the Catquest-9SF [38], measured at baseline and 3 months after first-eye surgery (Table 1).Health-related quality of life (HRQL) will be measured using two questionnaires: EuroQol’s EQ-5D-5L [39] and the Health Utilities Index Mark-3 (HUI-3) [40], measured at baseline, 1 week after first-eye surgery, 4 weeks after second-eye surgery and 3 months after first-eye surgery (Table 1).**Incremental cost-effectiveness ratios (ICERs)**: these will be expressed as 1) incremental societal costs per quality-adjusted life year (QALY) gained, 2) incremental healthcare costs per patient with postoperative refraction ≤1.0 D from target refraction, 3) incremental healthcare costs per clinically improved patient on the NEI VFQ-25 questionnaire, 4) incremental healthcare costs per clinically improved patient on the Catquest-9SF questionnaire, and 5) incremental healthcare costs per patient with clinical improvement in (un)corrected distance visual acuity. QALYs will be calculated based on generic HRQL.**Budget impact** will be reported as a difference in costs. Different scenarios will be compared to investigate the impact of various levels of implementation.

Adverse events are defined as any undesirable ophthalmic event occurring during the study, whether or not considered related to the trial procedure or the experimental intervention. All ophthalmic adverse events reported spontaneously by the patient or observed by the investigator or his staff will be recorded. Serious adverse events are defined as any untoward medical occurrence or effect that results in death, is life threatening (at the time of the event), requires hospitalisation or prolongation of existing inpatients’ hospitalisation, results in persistent or significant disability or incapacity, is a congenital anomaly or birth defect, or any other important medical event that did not result (but could have resulted) in any of the outcomes listed above due to medical or surgical intervention.

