### Study procedures

Visits are planned at baseline (preoperatively), and 1 week after first-eye surgery and 4 weeks after second-eye surgery. Patients will undergo study procedures as shown in Table 1. At 3 months after surgery, the occurrence of complications is derived from the patient record and patients will fill in the final questionnaires. Visual acuity will be measured by using the Early Treatment Diabetic Retinopathy Study (ETDRS) chart and measured refraction will be subjective (not automated).

**Table 1 Tab1:** Study procedures per follow-up time point

Assessment/ procedure	Visit					
	Preoperative	Surgery 1	1 week after surgery 1	Surgery 2 (if applicable)	4 weeks after surgery 2	3 months after surgery 1 (post/email)
Check for in−/exclusion criteria	X					
Informed Consent	X					
Medical history	X					
Check medication	X	X	X	X	X	X^a^
Ophthalmic examination	X		X		X	
Check adverse events		X	X	X	X	X^a^
Refraction	X		X		X	
CDVA	X		X		X	
NEI VFQ-25 questionnaire	X					X
Catquest-9SF questionnaire	X					X
EQ-5D-5L questionnaire	X		X		X	X
HUI-3 questionnaire	X		X		X	X
Cost questionnaire	X					X

^a^derived from the patient record and questionnaires

The intervention consists of bilateral cataract surgery by an experienced cataract surgeon. A standard phacoemulsification technique with intraocular lens implantation will be used. Surgery will be performed either during a single operating session (ISBCS) or during separate operating sessions with a minimum of 2 weeks apart (DSBCS), depending on randomisation. ISBCS will be performed in accordance with the “iSBCS General Principles for Excellence in ISBCS 2009”, treating both eyes as completely separate aseptic procedures in order to minimize the risk of bilateral endophthalmitis. For both ISBCS and DSBCS, intracameral antibiotics will be administered at the end of each operation. Topical antibiotics and anti-inflammatory drugs will be commenced postoperatively. After surgery, DSBCS patients will receive an eye patch and ISBCS patients will receive a transparent eye shield.

Patients can withdraw from the study at any time for any reason without any consequences. The investigator can decide to withdraw a patient from the study for urgent medical reasons. In case a patient withdraws from the study after randomization, the case is considered lost to follow-up, but will be included in the intention to treat analysis.

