#### Secondary outcomes

For secondary outcomes, data analyses will be performed as follows: presence of non-inferiority of ISBCS compared to DSBCS regarding the difference in the proportion of second eyes with a refractive outcome within ±0.5 D of target refraction will be evaluated similar to the method described under primary outcome. For visual acuity, presence of non-inferiority of ISBCS will be evaluated by comparing the proportion of patients with a corrected distance visual acuity (CDVA) 4 weeks after surgery of the second eye of ≤0.10 LogMAR between groups. The computed sample size of 858 patients for the primary outcome translates to an allowed non-inferiority margin of 10% to establish non-inferiority at the 0.05 alpha level regarding this secondary outcome measure. Corrected and uncorrected distance visual acuity in second eyes, patient-reported outcomes, and utilities will be analysed using a linear mixed model to test for overall differences between groups over time. The difference in the incidence of intraoperative and postoperative complications will be analysed using mixed-effects logistic regression to account for the fact that both eyes of each patient are included in the analysis and nesting of patients within centers.

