#### Cost-effectiveness analysis

A trial-based economic evaluation will be performed over a three-month time horizon (first-eye surgery until the final questionnaires at 3 months after first-eye surgery). A societal and healthcare perspective will be used and ICERs will be calculated for the outcome measures described earlier in this protocol. Uncertainty in the point estimates of the ICERs will be assessed using bootstrap analyses with 1000 replications. Based on these bootstrap analyses, cost-effectiveness acceptability curves will be constructed, to show the probability that the intervention is cost-effective for a range of threshold values of the ICER. Additional sensitivity analyses will be performed to investigate the impact of varying input parameters used in the cost-effectiveness analysis.

In addition to the trial-based economic evaluation, the lifetime economic impact of ISBCS compared to DSBCS will be investigated by means of a decision analytical model, in order to take rare events (e.g. bilateral complications) into account. The model-based economic evaluation will address the cost per QALY (societal perspective) and cost per patient with postoperative refraction within 1.0 D from target refraction (health care perspective). Input data for the model will be based on the data from the current study and from a literature review. We will express the model’s robustness and uncertainty by means of sensitivity analyses, confidence intervals, and by creating cost-effectiveness acceptability curves. Annual discount rates of 4 and 1.5% for costs and QALYs, respectively, will be used to determine the present value of costs and QALYs accrued over a lifetime.

In accordance with the Dutch guidelines for economic evaluations, the EQ-5D-5L will be used to determine QALYs using published Dutch tariffs [39]. In addition, the HUI-3 will be used because it is the only generic preference-based HRQL questionnaire that includes questions about vision [40].

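### The complication window runs from first-eye surgery, so second eyes in the delayed arm are observed for less time and have one scheduled examination fewer than second eyes in the same-day arm

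*Protocol article*

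**What the plan says.** All references are to the protocol article.

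- **Clock.** Outcome measures defines the complication outcome as "the number of intraoperative and postoperative complications within 3 months after first-eye surgery". The Abstract and the last column of Table 1 use the same origin. The text of Study procedures says only 3 months after surgery, without naming the eye.
- **Gap between eyes.** Study procedures has DSBCS done in "separate operating sessions with a minimum of 2 weeks apart (DSBCS"). The article states no upper limit. In ISBCS the gap is zero.
- **Examinations.** "Visits are planned at baseline (preoperatively), and 1 week after first-eye surgery and 4 weeks after second-eye surgery". Table 1 agrees and has no examination 1 week after a separate second operation.
- **Other capture.** At 3 months "the occurrence of complications is derived from the patient record", and Table 1 adds questionnaires as a source. Outside the visits, "All ophthalmic adverse events reported spontaneously by the patient or observed by the investigator or his staff will be recorded".
- **Model.** Secondary outcomes specifies "mixed-effects logistic regression to account for the fact that both eyes of each patient are included in the analysis", together with nesting of patients in centres. No time-at-risk term is mentioned.
- **Aim.** Objectives lists superiority of ISBCS on the incidence of complications as a secondary objective.

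**The concern.** Both eyes count equally in the analysis, but the clock starts with the first eye. A second eye is followed for the whole window in one arm and for the window minus the gap in the other. The visit schedule adds a second asymmetry: an ISBCS second eye is examined at 1 and 4 weeks after its operation, a DSBCS second eye at 4 weeks only. A binary outcome per eye cannot separate a lower risk from a shorter or less frequent look.

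The Background and Discussion give the risk of complications as a main reason why surgeons delay the second eye. If DSBCS second eyes are under-observed, equal true risks could look like an excess with same-day surgery, and a real advantage of ISBCS could be masked. The trial is also unblinded, so a difference that arises from observation would be hard to recognise afterwards.

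**Working it through.** **The plan's own figure.** The article gives no figure for complications. Its only computed figure is the sample size: 2 × 0.94 × 0.06 × (1.645 + 1.282)² / 0.05² ≈ 386.4 per group. This agrees with the stated 386, and 772 / 0.90 gives 858. Complications do not enter it, so it plays no part here.

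**Inputs.** Window: 3 months from first-eye surgery, taken as 13 weeks (assumption). Gap d: 0 in ISBCS and at least 2 weeks in DSBCS (Study procedures). Values of d above 2 weeks are assumptions.

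**Step 1: observation time.** DSBCS second-eye window = 13 − d. Eye-weeks per patient = 26 − d, against 26 in ISBCS.

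| Gap d (weeks) | Second-eye window (weeks) | Share of 13 | Eye-weeks, DSBCS/ISBCS |
|---|---|---|---|
| 2 | 11 | 85% | 24/26 = 0.92 |
| 4 | 9 | 69% | 22/26 = 0.85 |
| 8 | 5 | 38% | 18/26 = 0.69 |

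With a gap above 9 weeks the 4-week visit would fall after the window closes (d + 4 > 13).

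**Step 2: postoperative events lost through the window.** Eye-time is not the same as events. Let F(t) be the share of events with onset by week t after an eye's surgery. With equal true risk per eye, the DSBCS/ISBCS capture ratio over both eyes is [1 + F(13 − d)/F(13)] / 2. Under a constant hazard, F(t) is proportional to t. For early onset I take F(t) = 1 − exp(−t/τ), with τ the mean onset in weeks (assumption).

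| Onset | Loss, d = 2 | Loss, d = 4 | Loss, d = 8 |
|---|---|---|---|
| Constant hazard | 7.7% | 15.4% | 30.8% |
| τ = 4 | 1.3% | 3.5% | 12.9% |
| τ = 2 | 0.1% | 0.5% | 4.0% |
| τ = 1 | <0.1% | <0.1% | 0.3% |

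Example, τ = 2 and d = 4: F(9)/F(13) = (1 − e^−4.5)/(1 − e^−6.5) = 0.990, so the ratio is 0.995 and the loss 0.5%.

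**Step 3: the missing 1-week examination.** Let f be the share of events that only a 1-week examination would reveal (assumption). With equal windows, the ratio over both eyes is 1 − f/2.

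- f = 10%: ratio 0.95, apparent ISBCS/DSBCS ratio 1.05
- f = 25%: ratio 0.875, apparent ratio 1.14
- f = 50%: ratio 0.75, apparent ratio 1.33

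**Step 4: effect on a test.** Assume a true rate of 5% per eye in both arms, 2 × 386 = 772 independent eyes per arm, and a two-sided 5% test of two proportions. The chance of wrongly finding ISBCS worse is 2.5% with equal capture, 5.4% at a ratio of 0.923 (constant hazard, 2-week gap) and 8.4% at 0.875 (f = 25%).

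**Step 5: after the change.** With the same window and the same examination times counted from each eye's own surgery, the ratio is 1.00 at every gap.

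**The case against.** The strongest reply is that the shorter window may cost almost nothing. Intraoperative complications do not depend on the length of follow-up. The Background says that endophthalmitis mostly occurs within 2 weeks of surgery, which lies inside the window even at an 8-week gap. Table 1 lists the visit 4 weeks after surgery 2 before the 3-month contact, which suggests gaps below about 9 weeks, and a journal article may leave an upper limit to the full protocol. This stands. For early-onset events and short gaps the window effect is close to zero, and the absence of a stated maximum is not a fault in itself. Early onset does not help with the missing 1-week examination, however; it makes that examination more important.

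The second reply is that ascertainment also runs the other way. DSBCS patients have an additional adverse-event check at surgery 2. Their first eye is seen again at 6 weeks or later, against 4 weeks in ISBCS. Spontaneous reports, patient records and questionnaires feed the count in both arms. This stands too, as far as the net direction over both eyes is concerned. It does not make the second eyes comparable: the check at surgery 2 comes before that eye's postoperative course, and reports and records mainly catch events that cause symptoms or lead to care.

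Third, the stated aim for complications is superiority of ISBCS. An artefact that works against ISBCS would not produce a false claim in its favour. That is correct, and it limits the harm, but overstating harm or hiding a benefit would still mislead.

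**Conclusion.** The point holds in a limited form, as something that should be fixed. By design, DSBCS second eyes have at least 2 of about 13 weeks less observation and one scheduled examination fewer. For second eyes this works against ISBCS. The loss of DSBCS postoperative events through the window is about 0.5% or less for early onset (mean 1 to 2 weeks) with gaps of 2 to 4 weeks, and 7.7% under a constant hazard at a 2-week gap. It is larger with longer gaps or if some events show only at a 1-week examination. The onset patterns, gaps above 2 weeks, the share f and the 5% event rate are all assumptions.

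Three stronger readings are tempting, and the article does not support them.

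- **That the complication comparison is biased against ISBCS as a settled fact.** It is exposed to bias. Event timing and actual gaps are not given, and the net direction over both eyes is not established.
- **That DSBCS costs are understated in the same way.** The economic evaluation uses a "three-month time horizon (first-eye surgery until the final questionnaires at 3 months after first-eye surgery"), the same for every patient in both arms. That is a legitimate design. It may cut off late second-eye costs, but it also covers the time DSBCS patients wait for the second eye, and a lifetime model supplements it.
- **That the main conclusion is at risk.** The primary endpoint is timed at 4 weeks after second-eye surgery in both arms and is unaffected, as is the sample size.

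**What to change.** 1. In Outcome measures, define complications per eye in one fixed window from that eye's own surgery, equal in both arms (for example 3 months), and align the 3-month wording in Study procedures with it. The planned patient-record review then has to be extended for DSBCS second eyes. A full 3 months would need records to at least 13 + 2 = 15 weeks after surgery 1, and later with longer gaps. The same rule covers ISBCS patients whose second operation is postponed, a case that Statistical analysis foresees.
2. Because a longer record review does not replace the 1-week examination, add a sensitivity analysis restricted to findings at examinations that both arms share: first eyes at 1 week and second eyes at 4 weeks.
3. Leave the economic horizon as it is. A per-eye cost window would accrue DSBCS costs over 13 + d weeks against 13 for ISBCS, and would separate them from the QALYs and the cost questionnaire.

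The cost is a change of wording, a somewhat longer record review and one further analysis. DSBCS complication data close a few weeks later. No added study visit and no change in sample size are needed.

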### Randomisation and blinding

Study participants will be randomized to either ISBCS (intervention) or DSBCS (control). Each patient will receive a randomization number from a computerized random number generator. In a certified electronic data capture tool called Castor EDC [41], the subject number will be allocated to ISBCS or DSBCS through block randomisation stratified for center and axial length. Random varying block sizes of 2 and 4 will be used. Blinding is not possible because of the nature of the intervention.

### Sample size calculation

The sample size calculation is based on the proportion of patients with a postoperative refractive error in the second eye that deviates less than 1.0 D from target refraction. The only RCT thus far that reported this outcome showed that 91.0 and 90.3% of ISBCS and DSBCS eyes, respectively, was within 1.0 D [15]. Another (nonrandomized) comparative study showed that 96.8 and 97.0% of ISBCS and DSBCS eyes, respectively, was within 1.0 D [29]. Since no difference is expected with regard to this outcome, these percentages were averaged giving an expected proportion of 94% in both treatment groups. For the sample size calculation, it is assumed that the proportion in the ISBCS group is equal to or smaller than the proportion in the DSBCS group (i.e., non-inferiority). A non-inferiority margin of 5% is allowed (i.e., the proportion in ISBCS would need to be > 5% lower than the proportion in DSBCS to detect a statistically significant difference). The probability of a Type I error (alpha) is set at 0.05, and the probability of a Type II error (beta) is set at 0.10 (i.e., power is 90%). All sample sizes were calculated using an online 2-sample non-inferiority or superiority calculator for the comparison of two proportions (www.powerandsamplesize.com). The required sample size is 386 patients per group or 772 patients in total. Factoring in a loss to follow-up of 10% gives a final sample size of 858 patients.

### Statistical analysis

All data will be collected in a database (Castor) and will be exported to IBM SPSS Statistics (IBM, Armonk, NY, USA) for data analysis. The data analyses will be performed according to the intention to treat principle. However, considering that second-eye surgery can be delayed in ISBCS patients with complications during first-eye surgery, the analyses will be repeated based on a per protocol analysis. As recommended for non-inferiority trials in literature, both analyses will be performed and non-inferiority will be established if both analyses produce the same conclusion [42]. For all analyses, stratification variables (center and axial length) are accounted for by including them in the analysis model and significance levels will be set at 0.05.

#### Baseline characteristics

Baseline characteristics will be presented either as means with standard deviation and 95% confidence intervals, as median with interquartile range, or as frequencies (with percentages), as appropriate.

#### Primary outcome

With regard to the primary endpoint of refractive outcome, the difference in the proportion of second eyes with a refractive outcome ≤1.0 D of target refraction will be analysed using a logistic regression analysis with correction for stratification variables (center and axial length), where a logistic mixed model with center as random factor to account for the hierarchical nature of the data (patients are nested in centers) will be used as sensitivity analysis. To evaluate non-inferiority, a one-sided test procedure will be used. Non-inferiority will be established at the α = 0.05 significance level if the lower limit of a (1-2α)× 100% confidence interval (=90% CI) for the difference (ISBCS - DSBCS) is above the non-inferiority margin (δ) of − 5% [42]. Possible scenarios of observed treatment differences between ISBCS and DSBCS will be evaluated as reported by the CONSORT Statement 2010 [43].

#### Secondary outcomes

For secondary outcomes, data analyses will be performed as follows: presence of non-inferiority of ISBCS compared to DSBCS regarding the difference in the proportion of second eyes with a refractive outcome within ±0.5 D of target refraction will be evaluated similar to the method described under primary outcome. For visual acuity, presence of non-inferiority of ISBCS will be evaluated by comparing the proportion of patients with a corrected distance visual acuity (CDVA) 4 weeks after surgery of the second eye of ≤0.10 LogMAR between groups. The computed sample size of 858 patients for the primary outcome translates to an allowed non-inferiority margin of 10% to establish non-inferiority at the 0.05 alpha level regarding this secondary outcome measure. Corrected and uncorrected distance visual acuity in second eyes, patient-reported outcomes, and utilities will be analysed using a linear mixed model to test for overall differences between groups over time. The difference in the incidence of intraoperative and postoperative complications will be analysed using mixed-effects logistic regression to account for the fact that both eyes of each patient are included in the analysis and nesting of patients within centers.

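### The CDVA ≤0.10 LogMAR non-inferiority comparison names no baseline acuity term; adding the preoperative CDVA already collected would be a free but modest gain in precision

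*Protocol article*

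**What the plan says.** Secondary objective 2 (Objectives) is non-inferiority of postoperative visual acuity. The Secondary outcomes section settles it by "comparing the proportion of patients with a corrected distance visual acuity (CDVA) 4 weeks after surgery of the second eye of ≤0.10 LogMAR" between the groups, with an allowed margin of 10% at the 0.05 level.

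The Outcome measures section lists distance acuity in LogMAR at 1 week and 4 weeks as "corrected for baseline visual acuity". It then adds the proportion reaching 0.1 LogMAR as a further outcome, and does not repeat the baseline correction there.

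For every analysis, the Statistical analysis section states that "stratification variables (center and axial length) are accounted for by including them in the analysis model". No other covariate is named for the acuity proportion. Table 1 shows CDVA measured at the preoperative visit. Continuous CDVA in second eyes goes into a linear mixed model that tests for differences; no margin is attached to it.

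**The concern.** Preoperative acuity can be expected to predict postoperative acuity, and the plan treats it as worth correcting for when acuity is analysed in LogMAR. The one comparison that gives the non-inferiority verdict on acuity is described without it. Leaving a prognostic covariate out of a randomised comparison does not bias the result. It does make the confidence interval for the difference in proportions wider than the collected data require, and the interval decides the verdict. At stake is the precision of one secondary objective. The question is whether the loss is large enough to matter.

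**Working it through.** **Inputs from the article.** "The probability of a Type I error (alpha) is set at 0.05"; "To evaluate non-inferiority, a one-sided test procedure will be used", read from the lower limit of a 90% interval; power 90%; "giving an expected proportion of 94% in both treatment groups"; "A non-inferiority margin of 5% is allowed"; 386 evaluable patients per group; acuity margin 10 percentage points. The one-sided 90% interval is set out for the primary outcome, and I carry it over to acuity.

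**Assumptions, not in the article.** Success proportion p for CDVA ≤0.10 LogMAR: 85-90%, with lower values shown for power. Correlation r between preoperative and 4-week second-eye CDVA: 0.2 to 0.5. Both LogMAR values are taken as jointly normal, with equal true proportions in the two arms.

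**Step 1: the plan's own figures.** n per group = 2·p(1−p)·(z₀.₉₅+z₀.₉₀)²/δ² = 2 × 0.94 × 0.06 × 2.926²/0.05² = 386.4, against 386 stated. Then 772/0.90 = 857.8, so 858. For the 10-point acuity margin at p = 0.50, 2 × 0.25 × 2.926²/0.10² = 428.2, or 429 per group and 858 in total. The 10% margin therefore fits a 50% success rate with all 858 evaluable. That reading is inferred; the article does not state it.

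**Step 2: power as planned, without baseline CDVA.** SE = √(2p(1−p)/386) and power = Φ(0.10/SE − 1.645).
- p = 0.50: SE 0.0360, power 87%
- p = 0.66: SE 0.0341, power 90%
- p = 0.80: SE 0.0288, power 97%
- p = 0.85: SE 0.0257, power 98.8%
- p = 0.90: SE 0.0216, power 99.9%

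**Step 3: gain from adding preoperative CDVA.** With a standardised preoperative value b, the chance of success is Φ((z_p − r·b)/√(1−r²)). The share of outcome variance explained is R² = [Φ₂(z_p, z_p; r²) − p²]/[p(1−p)], where Φ₂ is the bivariate normal probability with correlation r². The variance of the standardised difference falls by the factor 1−R², so the gain in effective sample size is 1/(1−R²) − 1.

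| r | R², p = 0.85 | Gain | R², p = 0.90 | Gain |
|---|---|---|---|---|
| 0.2 | 0.0174 | 1.8% | 0.0141 | 1.4% |
| 0.3 | 0.0402 | 4.2% | 0.0331 | 3.4% |
| 0.4 | 0.0741 | 8.0% | 0.0621 | 6.6% |
| 0.5 | 0.1212 | 13.8% | 0.1037 | 11.6% |

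**Step 4: what that does to the verdict.** At p = 0.85 the half-width of the 90% interval is 1.645 × 0.0257 = 4.2 points. It becomes 4.2 × √(1−0.0402) = 4.1 at r = 0.3 and 4.2 × √(1−0.1212) = 4.0 at r = 0.5. Power at r = 0.5 moves from 98.8% to 99.4%. The covariate would matter most at a low success rate: at p = 0.50 and r = 0.5, R² = 0.161, the gain is 19%, and power rises from 87% to about 92%.

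**The case against.** The strongest reply is that the omission is read from silence. The statement on center and axial length says what every model will contain, not that nothing else may enter. The article condenses a full protocol (version 7.0), and the covariates of a secondary model may be set there or in the analysis plan. This stands in part. What can be said is that the article goes into covariates, names baseline correction for one form of the acuity outcome, and names none for the form that carries the verdict. If the full documents already include the term, only confirmation is needed.

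A second reply is that the test does not need the help. That also stands: Step 2 shows adequate power for the margin across the assumed range. Nor is a chance imbalance in preoperative acuity a bias, since the interval already allows for it.

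A reader might infer two stronger points, and the documents support neither.

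- **That Outcome measures and Secondary outcomes contradict each other on baseline correction.** They do not. The correction is attached to the LogMAR outcomes, and the proportion is introduced separately.
- **That cutting LogMAR at 0.10 undermines the verdict, so non-inferiority should be judged on mean LogMAR.** A cut-off does cost information. A 10-point fall from 85% equals a shift of 1.036 − 0.674 = 0.362 SD, which needs 2 × (2.926/0.362)² ≈ 131 per arm, against 218 for the proportion (2 × 0.85 × 0.15 × 2.926²/0.10²), a ratio of 60%. But a mean answers a different question from the proportion reaching a threshold. It would need a LogMAR margin, which the article does not give, and its estimate largely repeats the planned linear mixed model. A threshold outcome also matches the form of the primary endpoint.

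**Conclusion.** The point holds as an optional improvement to a secondary analysis. It is not an error and does not threaten validity. As described, the acuity non-inferiority comparison leaves out a prognostic value that is already collected. Including it would be worth about 1-2%, 3-4%, 7-8% or 12-14% more patients at r = 0.2, 0.3, 0.4 or 0.5. Those figures rest on assumed success of 85-90%, on normal LogMAR and on an assumed r, so the documents cannot fix the gain more closely. At such success rates the verdict would rarely change, because power already exceeds 98%.

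**What to change.** In Secondary outcomes, or in the analysis plan if it is silent, add preoperative second-eye CDVA as a continuous covariate beside center and axial length in the model for CDVA ≤0.10 LogMAR. The article does not name that model; a logistic model, as for the primary outcome, is assumed here. Take the value from the preoperative visit, not from the 1-week visit, which follows randomisation and first-eye surgery. Report the standardised (marginal) difference in proportions, ISBCS minus DSBCS, with its 90% confidence interval against the existing 10% margin. A conditional odds ratio from the adjusted model cannot be compared with a margin in percentage points. Make the change before the data are analysed.

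The cost is one model term and one line of text. The endpoint, margin, visits and sample size stay as they are.

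### As written, the mixed model for continuous second-eye visual acuity takes in the week-1 visit, when ISBCS second eyes have been operated and DSBCS second eyes have not

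*Protocol article*

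**What the plan says.** Four statements in the protocol article bear on this.

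- **Outcome and visits** (Outcome measures): corrected and uncorrected distance acuity in LogMAR are assessed "1 week after first-eye surgery and 4 weeks after second-eye surgery, corrected for baseline visual acuity". Table 1 schedules CDVA at the same two post-operative visits and at baseline.
- **Eye and model** (Secondary outcomes): "Corrected and uncorrected distance visual acuity in second eyes, patient-reported outcomes, and utilities will be analysed using a linear mixed model". The stated purpose is "to test for overall differences between groups over time". The sentence names neither the visits that enter the model nor a visit-specific contrast.
- **Timing of surgery** (Study procedures): ISBCS patients have both eyes done in one session. DSBCS patients are operated "during separate operating sessions with a minimum of 2 weeks apart (DSBCS), depending on randomisation".
- **Level** (Statistical analysis): for all analyses "significance levels will be set at 0.05", with centre and axial length in the model.

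A separate acuity analysis is also described under Secondary outcomes. It is a non-inferiority comparison of the share of patients reaching a CDVA of 0.10 LogMAR or better, fixed at 4 weeks after the second operation, with a 10% margin.

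**The concern.** The Objectives section asks about post-operative acuity. At the week-1 visit a DSBCS second eye has no post-operative acuity. If that visit contributes to the group effect, the test partly compares eyes after surgery with eyes awaiting it.

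Two misleading results become possible. The model may report a difference favouring ISBCS when the eyes end up equally good. Or an early advantage that exists only because ISBCS second eyes were operated sooner may offset a real ISBCS deficit at 4 weeks. The second matters most for UDVA. Uncorrected acuity reflects residual refractive error, and the Background and Discussion give refractive surprise as one of the two main reasons for caution about ISBCS. The article states no other between-group test for UDVA.

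**Working it through.** **Step 1. The plan's own figure.** The article gives no figure for the acuity model; the nearest is the primary-endpoint sample size, which supplies n. With 94% in both arms, a 5-point margin, one-sided alpha 0.05 and 90% power:

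n per arm = 2 × 0.94 × 0.06 × (1.645 + 1.282)² / 0.05² = 386.4

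The article states 386 per arm (772 in total), and 772 / 0.9 = 858. These figures reproduce, and 386 per arm is used below.

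**Step 2. State of the second eye at each acuity visit, treated as assigned.**

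| Visit | ISBCS second eye | DSBCS second eye |
|---|---|---|
| Baseline | cataract | cataract |
| 1 week after first operation | about 1 week post-operative | unoperated (second operation at 2 weeks or later) |
| 4 weeks after second operation | 4 weeks post-operative | 4 weeks post-operative |

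Only the last row compares like with like after surgery.

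**Step 3. What an overall effect estimates.** Write d1 and d4 for the ISBCS advantage in LogMAR at week 1 and at 4 weeks. With two equally weighted post-baseline visits:

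overall effect = (d1 + d4) / 2

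If final acuity is identical, d4 = 0 and the overall effect is half the week-1 gap.

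**Step 4. Size under assumed values.** The documents give no gap, SD or within-eye correlation. Take d1 = 0.10, SD = 0.15 at each visit, correlation ρ = 0.5 and n = 386 per arm.

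- Overall effect = 0.10 / 2 = 0.05 LogMAR
- SE = √(2 × SD² × (1 + ρ)/2 / n) = √(2 × 0.0225 × 0.75 / 386) = 0.0094
- z = 0.05 / 0.0094 ≈ 5.3

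**Step 5. Range.** Chance of p < 0.05 (two-sided) with d4 = 0 and 386 per arm, for SD 0.15 to 0.25 and ρ 0.3 to 0.6:

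| Assumed week-1 gap | Overall effect | Chance of significance |
|---|---|---|
| 0.05 | 0.025 | 34% to 82% |
| 0.10 | 0.05 | 87% to more than 99.9% |
| 0.20 | 0.10 | about 100% |

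A test of the 4-week contrast alone would reject at the nominal 5%.

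**Step 6. Group-by-time test.** The interaction estimates d1 − d4. With d4 = 0 and d1 = 0.10 it equals 0.10, with SE = √(2 × 2 × SD² × (1 − ρ) / n) = √(4 × 0.0225 × 0.5 / 386) = 0.0108 and z ≈ 9.3. Testing the interaction instead does not remove the problem.

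**Step 7. Masking.** Suppose ISBCS is 0.20 better at week 1 because DSBCS second eyes are unoperated, but truly 0.10 worse at 4 weeks. The overall effect is (0.20 − 0.10) / 2 = 0.05 in favour of ISBCS.

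**The case against.** The strongest reply has four parts.

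- **The visits in the model are not listed.** The Outcome measures item does not say which eye each acuity visit serves, so week 1 might be meant for first eyes. The wording about time is generic: the same sentence covers the NEI VFQ-25 and Catquest-9SF, which have one post-baseline measurement each. This stands as a caution: inclusion of week 1 is inferred from reading the sections together. But week 1 is a defined acuity visit, the model is stated to be for second eyes, and nothing excludes that visit. Treating baseline as a repeated outcome rather than a covariate would still leave week 1 in.
- **A mixed model with visit as a factor yields a 4-week difference, and contrasts may be set in a fuller document.** That is possible. The purpose this article does state, however, is an overall difference, which is not the 4-week contrast.
- **The acuity objective is already tested at the right time.** For CDVA this stands. A reader might infer that the plan has no sound acuity comparison; the 4-week non-inferiority test on the 0.10 LogMAR threshold shows otherwise. It does not cover UDVA.
- **Earlier second-eye recovery is a genuine consequence of ISBCS.** This also stands. The Discussion lists less time between surgeries and faster total recovery among the potential benefits. It is therefore wrong to call the whole week-1 difference an artefact. It misleads only when read as a difference in post-operative acuity.

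**Conclusion.** The point holds as a moderate issue in a secondary analysis. Followed as written, the test for continuous second-eye CDVA and UDVA mixes a valid 4-week comparison with a surgery-timing difference, whether the main effect or the interaction is used. It can produce a difference favouring ISBCS when 4-week acuity is the same, and it can hide a 4-week deficit in UDVA.

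The figures of 0.05 LogMAR and z about 5.3 rest on an assumed week-1 gap, SD and correlation, equal visit weights and identical final acuity. They show what follows if week 1 enters the model, not what the trial will find.

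A reader might go further and conclude that the test is bound to favour ISBCS, or that the trial's main conclusion is at risk. The documents support neither. The size and even the direction of the overall effect depend on the 4-week difference as well, and the model's contrasts are not spelled out. Nor is every ISBCS second eye operated by week 1, since the Statistical analysis section allows for delay after a complicated first operation. The primary endpoint, the 0.5 D endpoint, the sample size and the 4-week CDVA non-inferiority test are unaffected.

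**What to change.** Add to the Secondary outcomes section that the inferential contrast for second-eye CDVA and UDVA is the group difference at 4 weeks after second-eye surgery, adjusted for that eye's baseline acuity, centre and axial length. If the mixed model is kept, make this its only tested contrast for second eyes. Use the week-1 visit to compare first eyes, which are at the same post-operative stage in both arms. Report week-1 second-eye acuity descriptively, labelled as an effect of surgery timing.

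The cost is a sentence or two of text. No data, visits or patients are added.
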